# The EPIPHA-KNEE trial: Explaining Pain to target unhelpful pain beliefs to Increase PHysical Activity in KNEE osteoarthritis – a protocol for a multicentre, randomised controlled trial with clinical- and cost-effectiveness analysis

**DOI:** 10.1186/s12891-021-04561-6

**Published:** 2021-08-28

**Keywords:** Osteoarthritis, Physical activity, Exercise, Walking program, Strengthening program, Pain science education, RCT, Physiotherapy

## Abstract

**Background:**

Despite well-established benefits of physical activity for knee osteoarthritis (OA), nine of ten people with knee OA are inactive. People with knee OA who are inactive often believe that physical activity is dangerous, fearing that it will further damage their joint(s). Such unhelpful beliefs can negatively influence physical activity levels. We aim to evaluate the clinical- and cost-effectiveness of integrating physiotherapist-delivered pain science education (PSE), an evidence-based conceptual change intervention targeting unhelpful pain beliefs by increasing pain knowledge, with an individualised walking, strengthening, and general education program.

**Methods:**

Two-arm, parallel-design, multicentre randomised controlled trial involving 198 people aged ≥50 years with painful knee OA who do not meet physical activity guideline recommendations or walk regularly for exercise. Both groups receive an individualised physiotherapist-led walking, strengthening, and OA/activity education program via 4x weekly in-person treatment sessions, followed by 4 weeks of at-home activities (weekly check-in via telehealth), with follow-up sessions at 3 months (telehealth) and 5 and 9 months (in-person). The EPIPHA-KNEE group also receives contemporary PSE about OA/pain and activity, embedded into all aspects of the intervention. Outcomes are assessed at baseline, 12 weeks, 6 and 12 months. Primary outcomes are physical activity level (step count; wrist-based accelerometry) and self-reported knee symptoms (WOMAC Total score) at 12 months. Secondary outcomes are quality of life, pain intensity, global rating of change, self-efficacy, pain catastrophising, depression, anxiety, stress, fear of movement, knee awareness, OA/activity conceptualisation, and self-regulated learning ability. Additional measures include adherence, adverse events, blinding success, COVID-19 impact on activity, intention to exercise, treatment expectancy/perceived credibility, implicit movement/environmental bias, implicit motor imagery, two-point discrimination, and pain sensitivity to activity. Cost-utility analysis of the EPIPHA-KNEE intervention will be undertaken, in addition to evaluation of cost-effectiveness in the context of primary trial outcomes.

**Discussion:**

We will determine whether the integration of PSE into an individualised OA education, walking, and strengthening program is more effective than receiving the individualised program alone. Findings will inform the development and implementation of future delivery of PSE as part of best practice for people with knee OA.

**Trial registration:**

Australian New Zealand Clinical Trials Registry: ACTRN12620001041943 (13/10/2020).

**Supplementary Information:**

The online version contains supplementary material available at 10.1186/s12891-021-04561-6.

## Background

Osteoarthritis (OA) is increasingly prevalent in older adults [1] and has a large personal health and societal burden [2]. The knee is the most common joint affected by OA and is the most disabling [1], making it essential to find ways to promote long-term health, quality of life, and reduced pain and disability in this population.

Regular structured physical activity (aerobic or strengthening exercise) reduces pain and disability in people with knee OA [3, 4], even in those with severe, end-stage OA who are awaiting joint replacement [5]. Recommended by all clinical guidelines as a core treatment for knee OA, structured physical activity has similar effects on pain and disability as commonly used drugs, but without the pharmacological side effects (e.g., gastrointestinal problems) [3, 4]. Importantly, even relatively small improvements in physical activity levels predict improved function [6] and reduced disability [7] in those with knee OA. Despite this, the majority of people with OA are inactive [8]. Only 13% of people with OA meet physical activity guidelines for moderate-vigorous activity (150 min/week) and only 19% meet suggestions of ≥10,000 steps/day [8]. While most people in the general public do not meet recommended activity levels, people with OA are still 25% less active than those without OA [8]. Low physical activity levels also have serious health implications for people with knee OA: cardiovascular mortality risk in those with OA is nearly double that of the general population and is highest for those with the greatest walking disability [9].

Recent literature supports that unhelpful beliefs likely contribute to inactivity in those with knee OA. For example, in people with OA, those who are inactive are more likely than those who are active to believe that they are physically unable to exercise and that physical activity is unsafe [10, 11]. Further, people with knee OA often focus heavily on pain and hold beliefs that OA is an incurable, progressive ‘bone-on-bone’ disease, caused by ‘wear-and-tear’ [12, 13]; perspectives refuted by contemporary scientific evidence [14–18]. Given such beliefs, it is perhaps unsurprising that people with knee OA generally report increased levels of fear of movement itself and of movement-induced injury [19, 20] and report uncertainty as to whether undertaking physical activity will be helpful for them [21]. Unfortunately, these unhelpful beliefs are also held by many health care professionals, who reinforce consumers’ misunderstandings, further compounding the problem. For example, many clinicians believe that structured physical activity is not appropriate for all people with knee OA (i.e., not appropriate for people with severe OA) and that physical activity can be harmful [22]. Such consumer and clinician beliefs contrast with high-quality research showing that physical activity does not further damage the joint [3, 23], and that activity is helpful even in those with end-stage OA awaiting joint replacement [5]. Critically, in people with knee OA, such unhelpful beliefs negatively influence their decision to engage with structured physical activity [12] and reduce their participation in activities that may be pain-provoking [24]. Ultimately, negative beliefs about OA and activity are predictive of lower future physical activity levels in those with knee OA [25].

Current strategies that aim to increase physical activity in people with OA include structured physical activity interventions targeting aerobic capacity, endurance, and strength [26]. These interventions aim to increase exercise tolerance, strength or overall fitness, maintain or reduce weight, and decrease pain. They have short-term but not long-term effects on physical activity levels [26]. Behavioural interventions, targeting features such as self-efficacy or coping skills to promote self-management, have also been used to increase physical activity. Again, physical activity levels increase in the short term, but decline over time, with no effect after 12 months [27]. Critically, the reduction in benefits from physical activity in OA is directly related to declining rates of adherence [28]. Thus, improving long-term adherence is key to achieving meaningful health and OA-specific benefits. Promoting maintenance of physical activity gains remains a significant challenge – we are still chasing the holy grail of instilling physical activity as a regular part of daily life in people with OA.

A notable similarity amongst most current approaches that aim to increase physical activity is encouraging ‘movement despite pain’ (e.g., behavioural interventions using coping skills), with the ‘promise’ of pain-relieving effects over time. Arguably, such approaches may seem counterintuitive to people with knee OA as long as they consider pain to be a marker of joint damage [29]. For instance, if people believe that increases in pain represent more joint damage and that physical activity may be unsafe for their joint, then it is unlikely that they will engage in or adhere to activity programs that suggest that they should move despite having pain [12]. Further, if these unhelpful beliefs are not challenged, then flare-ups of pain that often occur with activity programs may derail long-term adherence [30]. Although including general education within physical activity programs is recommended by OA practice guidelines [31], we contend that current education may be suboptimal. Current education largely focuses on how to accurately and safely perform activity and the health and OA-specific benefits of activity [32]. Such education does not improve poor long-term activity adherence [33].

Contemporary pain science education (PSE) was developed to shift the meaning of pain from that of a marker of tissue damage to that of a need to protect the body from real or perceived danger or threat. PSE aims to re-conceptualise what pain *means* to someone [29]. It is distinct from cognitive therapy because it uses re-conceptualisation of the biological underpinnings of pain to enable a move away from thinking that only structural pathological factors contribute to pain. PSE also prioritises an understanding of the considerable central nervous system adaptations that occur when pain persists and the impact of these changes on the relationship between pain and true tissue threat. PSE therefore, provides a scientific basis for both a biopsychosocial model of pain and disability (i.e., underscoring that numerous factors can contribute to the experience of pain), and the enhanced sensitivity generated by central nervous system adaptations that occur as pain persists [29]. Importantly, PSE also differs fundamentally from current self-management education programs that aim to educate people with OA about physical activity benefits and behavioural modifications (and which have been shown to have no benefit in OA [34]), in that PSE targets the knowledge and beliefs that underlie behaviour [29]. With PSE, re-conceptualisation of pain is key: those with the greatest improvement in pain-related knowledge with PSE show the greatest immediate *and sustained* movement improvements [35].

High level evidence, including meta-analyses and randomised controlled trials (RCTs), shows that PSE increases pain knowledge, reduces unhelpful pain beliefs [35, 36], and improves pain, function, and disability (including physical activity levels) in various musculoskeletal pain conditions [35–41]. However, knee OA-specific data are lacking. We undertook a feasibility pilot study of a PSE-driven individualised education and walking program for people with knee OA [42]. The OA PSE intervention drew from established ‘Explain Pain’ programs (originally developed for back pain; see Moseley & Butler for an overview [29]), that were then modified to include contemporary understanding of the science of OA [16, 17, 43], including the impact of movement and loading of the knee joints [15, 18, 44]. The PSE intervention had high levels of participant-rated credibility and acceptability, with promising effects on pain knowledge and clinical outcomes of pain, function, and physical activity levels [42]. Our findings supported transition to a full trial after undertaking small methodological changes, and including a lower limb strengthening component to be consistent with best practice care [31].

Therefore, the aim of this study is to determine the clinical- and cost-effectiveness of a PSE-driven individualised walking, strengthening and education program, called EPIPHA-KNEE, in people with painful knee OA. We will compare EPIPHA-KNEE to an individualised walking, strengthening, and general OA educational program that is consistent with current best practice, using a randomised controlled trial (RCT). We hypothesise that the EPIPHA-KNEE intervention will lead to greater improvements in long-term physical activity levels and OA knee symptoms (pain, function, and stiffness) and will be cost-effective.

## Methods

### Design

EPIPHA-KNEE is a two-arm, multicentre, superiority RCT. Figure 1 outlines the phases of the RCT. This protocol has been developed according to the SPIRIT recommendations [45]. The intervention is described according to the TIDieR checklist [46]. The trial was prospectively registered with the Australian New Zealand Clinical Trial Registry (ACTRN12620001041943; https://bit.ly/2SfVySS). The trial is conducted at the University of South Australia and the University of Melbourne, with cost-effectiveness analysis led by health economists at Flinders University, Australia.

**Fig. 1 Fig1:**
[figure not shown]
Participant flow through the randomised controlled trial

### Participants

Participants aged ≥50 years with painful knee OA that has been present for at least 6 months, who have at least moderate levels of pain (≥4 on an 11-point Numerical Pain Rating Scale [47]) and who report at least moderate difficulty with daily activities [48] will be eligible for this trial. Table 1 provides the full inclusion and exclusion criteria. Our target sample size is 198 participants. Participants are recruited from the general community in Adelaide and Melbourne, Australia using advertisements placed in newspapers and relevant newsletters (e.g., Arthritis SA, Senior’s Living), as well as via social media (Facebook, Twitter).

**Table 1 Tab1:** Participant eligibility criteria

Inclusion criteria	Exclusion criteria
Fulfil the National Institute for Health and Care Excellence (NICE) clinical criteria for osteoarthritis: • Age ≥ 50 years;^a^ • Have activity related joint pain; and • Have morning stiffness ≤30 min.	Health conditions that prevent safe participation in physical activity interventions as listed in the American College of Sports Medicine Guidelines (e.g., cardiac or lung disease)
Average knee pain intensity (overall and/or while walking) of ≥4 on 11-point numeric rating scale (NRS, where 0 = no pain; 10 = worst pain possible) in the past week	For those identified as at risk from the pre-exercise screening, general practitioner does not give medical clearance
Moderate disability due to the knee over the past week (≥ 3 on the Global Disability Rating Scale)	Pain in other body areas that currently limits walking ability (e.g., back pain, foot pain, hip pain)
Knee pain of at least 6 months duration	Neurological disorders affecting lower limb movement (e.g., multiple sclerosis or stroke)
Current levels of moderate/vigorous physical activity (MVPA) below physical activity guideline recommendations (< 150 min/week of MVPA; assessed using the Active Australia Physical Activity Questionnaire)	Inflammatory arthritis (including rheumatoid arthritis)
Current purposeful walking for exercise of ≤30 mins/day on ≤5 days/week	Fibromyalgia
Able to give informed consent and to participate fully in the interventions and the assessment procedures	Planned knee replacement/surgery (next 12 months); and/or recent knee replacement on the non- or less-painful knee (< 6 months)
	Previously operated knee is the most painful knee
	Intra-articular therapy use in the 12 weeks preceding enrolment
	Any condition impacting decision-making/memory (e.g., Alzheimer’s, dementia)
	Severe depression (> 17 on the 4-item PROMIS depression subscale)
	Current moderate/vigorous physical activity levels above guideline recommendations (≥150 min/week; assessed using the Active Australia Physical Activity Questionnaire)
	Current purposeful walking for exercise of ≥30 mins/day on ≥5 days/week.
	Currently undergoing regular, active intervention for the knee (e.g., seeing a physiotherapist)
	Unable to commit to study requirements (unable to attend study appointments or complete study outcomes)

^a^Note: NICE criteria for age is > 45 years; however, ≥ 50 years has been used for the present trial to limit inclusion of younger participants with trauma-induced OA

Trial coordinators at the University of South Australia and the University of Melbourne manage the screening of volunteers, using a two-step process: i) via an online survey using REDCap (Research Electronic Data Capture) [49] and, if eligible, ii) via in-depth telephone screening by the site-specific trial coordinators. Additional clearance to participate is sought from a general practitioner for anyone who does not pass exercise safety screening questions. The study interventions are undertaken at private, community physiotherapy clinics and provided by designated, trained trial physiotherapists.

### Data collection and management

Data are collected via: paper or online questionnaires completed by the participant (self-reported outcomes); paper and online data forms completed by the research personnel (objective assessment data); and accelerometry data from a wrist-worn monitor (assessment of physical activity levels). All online questionnaires/data forms are completed in REDCap. Paper questionnaires are stored in a locked cabinet and the data are manually entered into REDCap (self-reported outcomes) or double-entered into an excel spreadsheet (objective assessment data) by an outcome assessor. All digital data (questionnaires, objective assessment data forms, accelerometry data) are stored on a secure password-protected server. For all data collection, the ‘study knee’ is the painful knee, or in those with bilateral symptoms, the most painful eligible knee. If pain levels are similar bilaterally, the right knee is considered the study knee.

### Randomisation allocation concealment and blinding

Following completion of the baseline assessments (questionnaires, objective assessment, accelerometry), participants are randomised to either the EPIPHA-KNEE group or the Best Practice Education/Activity Control group. The computer-generated randomisation schedule was prepared by the study biostatistician using Research Randomizer [50], with randomly selected permuted blocks of varying size (4 and 6) and using a 1:1 ratio to the two treatment groups within four strata (sex and site: Adelaide, Melbourne). The EPIPHA-KNEE intervention and the Best Practice Control intervention are provided by different physiotherapists located at different clinic sites. Thus, once allocated to an intervention group, participants choose one of the candidate physiotherapy clinics that provide that intervention to attend (i.e., the clinic that is most convenient for them).

Allocation is concealed using central automated allocation, with security in place to ensure data cannot be accessed or influenced. The randomisation schedule is stored within a password-protected electronic system (REDCap). A hard copy of the raw randomisation schedule is also stored in a secure location at each site should the electronic system fail. Only the unblinded Research Leads ([name] in Adelaide, KB in Melbourne) have access to raw copies of the randomisation schedules. The trial coordinators at each site (Adelaide, Melbourne), randomise participants to intervention group. Notably, while the trial coordinators determine if a participant is eligible for inclusion in the trial, due to inaccessible online randomisation with use of randomly permuted block size and stratification, they are unaware when this decision is made to which group the participant will be allocated. Once randomised, the (now) unblinded trial coordinators at each site (Adelaide, Melbourne) coordinate treatment appointment scheduling with the appropriate physiotherapist as identified by the participant.

Many of the primary and secondary outcomes are self-report questionnaires, thus participants are also assessors for these outcomes. Participants are advised that they will be randomised to receive one of two active physiotherapy treatments involving education and exercise that aim to improve overall health (i.e., limited disclosure). The exact details of the interventions are not provided prior to randomisation. After randomisation, participants are provided only with details of the intervention they receive. Given that both groups receive active treatments and that the primary outcomes of the trial are not disclosed, we anticipate that this will be sufficient for blinding the participants to group assignment. At study completion, participants are asked to guess which group they were in (intervention group of interest or control group) in order to assess participant blinding.

For objective outcomes assessed in-person at baseline and at 12 weeks, research personnel whose roles are independent of treatment allocation and delivery (i.e., blinded to group allocation) act as the outcome assessors. Participants are explicitly instructed not to discuss their intervention or treating therapist with the outcome assessor. The same assessor evaluates the baseline and 12-week outcomes for each participant. To formally evaluate assessor blinding, the assessors are asked to guess which group the participants were in (intervention or control) after the participant’s 12-week objective assessment.

Treating therapists are unavoidably aware of the intervention they provide, but each therapist is assigned to deliver only one intervention only, and both groups are providing an active intervention. Our goal is to have therapists of both groups believe they are providing the intervention of interest; this will be formally assessed at completion of the trial. Regardless, therapists will not be involved in any outcome assessment. An independent, blinded statistician will perform data analyses.

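### Coordinators who decide eligibility also randomise and learn each arm, so blocks of 4 and 6 leave the next allocation partly guessable (about 52–69%)

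*Protocol article*

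**What the plan says.** Under Participants, the Protocol article describes two screening steps: an online survey, then a second step "via in-depth telephone screening by the site-specific trial coordinators".

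Under Randomisation allocation concealment and blinding it sets out the rest:

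- **Randomising.** "The trial coordinators at each site (Adelaide, Melbourne), randomise participants to intervention group".
- **Unblinding.** "Once randomised, the (now) unblinded trial coordinators at each site (Adelaide, Melbourne) coordinate treatment appointment scheduling" with the physiotherapist concerned. The two interventions are "provided by different physiotherapists located at different clinic sites", so a booking reveals the arm.
- **Schedule.** Allocation is 1:1, with "randomly selected permuted blocks of varying size (4 and 6"), within four sex-by-site strata. Each site therefore runs two sequences, one for men and one for women.
- **Assurance.** The section accepts that, "while the trial coordinators determine if a participant is eligible for inclusion in the trial", the same people randomise. It says they still do not know the coming group, for three reasons: the online list cannot be accessed, block size varies, and randomisation is stratified.
- **Timing.** Randomisation follows completion of the baseline questionnaires, objective assessment and accelerometry. Under Primary outcomes, accelerometry covers 7 consecutive days.

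**The concern.** An inaccessible list stops anyone reading ahead. It does not stop someone who knows the past allocations from predicting the next one, and permuted blocks make that easier because each block must return to balance. The other two reasons in the assurance were meant to close this gap. Stratification cannot, because the coordinator knows each participant's sex and site. Whether mixing blocks of 4 and 6 does so is a matter of arithmetic.

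What is at stake is selection at entry. Someone who can guess the next arm may, knowingly or not, treat borderline or more committed volunteers differently, or alter when or in what order they are randomised. Commitment plausibly affects both step count and self-reported WOMAC. Blinding assessors and the statistician afterwards cannot undo selection at entry, and adjusting for sex and site does not remove differences in motivation.

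**Working it through.** The article gives no predictability figure, so there is none to reproduce.

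**Inputs.** From the article: blocks of 4 and 6, 1:1, four strata, 198 participants, and a target of d = 0.5 with 90% power. Assumed: the two block sizes are equally likely, and strata are even, at about 198/4 ≈ 50 each.

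**Step 1: the next assignment, all earlier ones in the stratum known.** The rule is to guess the arm with fewer allocations so far and to toss a coin at balance. The expected number of correct guesses in a block of size 2m is m + (2^(2m)/C(2m,m) − 1)/2.

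- Block of 4: 2 + (16/6 − 1)/2 = 2.833, and 2.833/4 = 70.8%.
- Block of 6: 3 + (64/20 − 1)/2 = 4.1, and 4.1/6 = 68.3%.
- Equal mix: (2.833 + 4.1)/10 = 69.3%.

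Full enumeration of both blocks agrees. Simulating 2,000 strata of 50 gives 69.0%. Mixing the sizes thus gains about 1.5 percentage points over fixed blocks of 4, because the rule uses only the running imbalance and not the block boundaries. A best-possible guesser who also knows the sizes gets the same 69.0%, although about 5.7% of assignments then become certain.

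**Step 2: the eligibility decision.** This comes at least a week before randomisation. Anyone in the same stratum who has been accepted but not yet randomised takes the next slot, and that allocation is unknown. The same simulation gives the hit rates in the table below.

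**Step 3: illustrative bias.** Suppose, as an assumption, that a guess shifts the expected outcome of the person enrolled by +s or −s SD according to the arm guessed. With hit rate p, each arm's mean moves by s(2p − 1) in opposite directions, so the bias is 2s(2p − 1). At 90% power, d = 0.5 corresponds to a non-centrality of 1.96 + 1.28 = 3.24. A bias b therefore gives 3.24 × b/0.5. For s = 0.1 and p = 0.69:

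- b = 2 × 0.1 × 0.38 = 0.076 SD.
- Non-centrality = 3.24 × 0.076/0.5 = 0.49.
- Two-sided rejection rate = P(Z > 1.47) + P(Z < −2.45) ≈ 7.8%.

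| Same-stratum participants waiting | Correct guesses | Bias if s = 0.1 | Type I error |
|---|---|---|---|
| 0 | 69% | 0.076 SD | 7.8% |
| 1 | 59% | 0.036 SD | 5.6% |
| 2 | 56% | 0.024 SD | 5.3% |
| 3 | 52% | 0.008 SD | 5.0% |

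With s = 0.05, even a 69% hit rate gives 0.038 SD and 5.7%.

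**Step 4: a less predictable scheme.** Take coin-tossing with a maximum imbalance of 4 and 50 per stratum. The exact calculation has 11% of assignments forced. The hit rate is 0.11 + 0.89 × 0.5 = 55.5%, or about 56%.

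**The case against.** The strongest reply is that this is a recognised safeguard and not an open list. Allocation is central and automated, coordinators cannot reach the schedule, and only the Research Leads hold raw copies. Guessing better than chance is not the same as knowing. That stands: the documents support a finding of predictability, not of failed concealment, and nothing suggests that anyone has steered entry.

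A reader might take 69% as the rate at which eligibility decisions can be informed. The documents do not support that, because baseline testing lies between the two and each waiting participant lowers the rate. The 69% applies at eligibility only when nobody in the stratum is waiting. Otherwise it applies only to discretion over whether, when or in what order to randomise after baseline, and the article describes no such discretion.

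The room for judgement at screening is also limited. Most criteria are thresholds, at-risk volunteers need medical clearance from a general practitioner, and the exclusion for inability to commit is defined as being unable to attend appointments or complete outcomes. In addition, the analysis contrasts change from baseline, so selection on baseline level largely cancels; the shift would have to be in later change. These points reduce the likely bias but do not remove the route to it.

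Three further inferences are tempting and go beyond the text:

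- **Block sizes published during recruitment.** This rests on the present tense; no recruitment dates are given. Publication would not raise the average hit rate in any case.
- **One coordinator per site.** The article does not give the number.
- **Knowledge of every earlier allocation.** This needs a single coordinator or shared knowledge within the site.

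**Conclusion.** The concern holds in a limited form. Of the three reasons offered for coordinators being unaware of the coming group, only the inaccessible list does real work. Stratification adds nothing, and varying the block between 4 and 6 adds almost nothing. Predictability is about 69% for the next assignment in a stratum and about 52–69% at the eligibility decision. These figures assume equally likely block sizes, about 50 per stratum, knowledge of all earlier allocations, and zero to three participants waiting. Accrual rate and the number of coordinators are not stated, so the range cannot be narrowed.

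The bias of 0.008–0.076 SD (about 2–15% of d = 0.5) and the type I error of 5.0–7.8% depend wholly on the assumed 0.1 SD shift. It would be wrong to quote the roughly 8% alone as the trial's error rate: it is the upper end of an illustration. The case for action is that the exposure can be removed cheaply, not that bias has been shown.

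**What to change.** For participants not yet randomised, separate the roles using existing staff. Someone who does not decide eligibility at that site, for example the other site's coordinator or the already unblinded Research Lead, should trigger randomisation and book the arm-specific clinic. The same person should receive therapist contacts and adverse-event reports. The section on dealing with adverse events sends those to the study coordinator, and because therapists are arm-specific, moving only the randomisation step would still let the history leak back.

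Optionally, generate the unused part of the schedule with a less predictable restricted scheme in the same four strata, and withhold its parameters until recruitment closes. A maximum imbalance of 4 lowers correct guesses to about 56%. However, the 11% of assignments that are forced would be certain to anyone who knew the limit, against about 5.7% now, so this should accompany role separation and not replace it.

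If recruitment has closed, correct the assurance under Randomisation allocation concealment and blinding, and report who knew earlier allocations when deciding eligibility.

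The cost is some cross-site coordination. If the schedule is replaced, there is also a documented mid-trial change and a slightly larger possible imbalance within a stratum, which the planned adjustment for sex and site covers. Sample size, strata, outcomes and analysis are unchanged.
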